## Abstract

**Introduction:**

The coronavirus disease pandemic has worsened psychological distress in people experiencing homelessness (PEH). This study evaluates the impact of learning the Bhagavad Gita versus engaging in Kuchipudi dance on reducing psychological distress in PEH in Chennai and Dhanbad, India.

**Methods and analysis:**

Participants will be allocated into Bhagavad Gita, Kuchipudi dance, Both interventions, or Control groups. The Kessler scale (K10) score, representing the primary outcome, will be measured at four time points: one day before intervention, one day after intervention completion, 40 days post-intervention, and 1 year post-intervention. The K10 scores will be analyzed using the Generalized Estimating Equation framework. Additionally, subgroup analysis based on participant demographics (e.g., age, education, religion, employment) will be conducted to explore potential differential effects using analysis of covariance. Statistical significance will be determined at p < 0.05 (two-tailed).

**Dissemination:**

After study completion, findings will be shared at conferences, in peer-reviewed journals, and with stakeholders and community groups. Authorship will be granted to contributing researchers, with acknowledgment for others. The dataset will be publicly available upon publication. Efforts will be made to communicate results through infographics, plain language summaries, and tailored strategies, including community meetings and digital platforms, to engage and empower PEH in decision-making.

**Trial registration:**

The trial has been registered with the Clinical Trials Registry of India (registration number: CTRI/2022/12/048416).

## Introduction

The COVID-19 pandemic has had a profound impact on the mental health of people experiencing homelessness (PEH) [1, 2] PEH have reported increased rates of anxiety, depression, and post-traumatic stress disorder [1, 2], with a significant proportion suffering from severe mental illness and chronic substance use [2]. Moreover, social isolation during the pandemic has been associated with heightened anxiety and depression symptoms among PEH [2]. Substance use, which is prevalent in this population, can further worsen mental health outcomes [2, 3].

The World Health Organization (WHO) defines mental health as a state of well-being, encompassing an individual’s ability to realize their potential, cope with life’s challenges, work productively, and contribute to their community [4]. Recognizing the importance of mental health, the WHO has advocated for integrating mental health support into the global response to the COVID-19 pandemic [5]. General guidance from the WHO on integrating mental health support into the pandemic response which can be applied to PEH includes providing social support, accurate information, and addressing stigma and discrimination.

Samanjasa Foundation has been actively engaged in providing services to PEH in Chennai, Dhanbad, Bhubaneshwar, and Hyderabad, India, for the past decade. These services include offering meals, upskilling opportunities, recreational activities, and linkages to government schemes and employment prospects. During the COVID-19 lockdown in India, we continued to support PEH by providing online recreational and upskilling activities. However, due to logistical challenges, we were unable to resume face-to-face sessions after the lockdown was lifted. Throughout our interactions with PEH, we observed an increase in psychological distress during and after the pandemic. To address this issue, we decided to augment our usual recreational activities, such as Kuchipudi dance classes [6], with an emic intervention involving imparting the teachings of the Bhagavad Gita through online platforms [7].

Engaging in hobbies has been shown to effectively reduce stress, foster social connections, and restore a sense of self among PEH [8, 9]. However, many of our clients have been unable to participate in recreational activities due to their daily struggles to earn a living, despite expressing a desire to engage in hobbies. Therefore, we sought a brief intervention that could enhance the coping abilities of PEH.

Findings from a previous study revealed that turning to religion emerged as a significant coping strategy for PEH, assisting them in managing the mental stress induced by the COVID-19 pandemic [10]. Building on this crucial insight, we posit that a religious and spiritual Intervention (RSI) could offer valuable support to PEH.

A notable systematic review and meta-analysis focused on RSIs in randomized clinical trials (RCTs) has underscored the potential of RSIs in enhancing mental health outcomes; however, this review exclusively encompassed studies affiliated with Islamic, Christian, and Jewish traditions [11]. The meta-analysis unveiled significant positive effects of RSIs on anxiety, general symptoms, and depressive symptoms. Nonetheless, due to the omission of any clinical trials focusing on the efficacy of Hindu RSIs or the impact of RSIs on individuals adhering to Hindu beliefs, a gap persists in understanding the benefits of Hindu RSIs, particularly among those embracing Hindu beliefs.

It is noteworthy that Hinduism is the most commonly practiced religion in India and there exist no empirical studies evaluating the effectiveness of Hindu RSIs. Therefore, tailoring an RSI to the Hindu context, especially in PEH, in the absence of empirical studies investigating the impact of Hindu RSIs, is a critical knowledge gap. Given the significant reliance on religious coping mechanisms among PEH [10]. and the dearth of research in this domain, our study aims to fill this void by specifically exploring the impact of learning the Bhagavad Gita—an essential Hindu scripture—as a potential RSI to alleviate psychological distress among PEH. This novel approach is informed not only by previous qualitative findings [10] but also by the imperative to address the unique needs of this population through culturally relevant interventions.

The Bhagavad Gita offers practical guidance on navigating daily stressors [12]. Within the realm of RSIs, recent studies offer insights into the potential relevance of the Bhagavad Gita’s teachings for psychological well-being among adolescents [13] and individuals coping with chronic illnesses [14]; however, these studies do not encompass a synthesis of empirical data to validate their findings. Recently, Das and Behura proposed that learning the Bhagavad Gita could improve the stress coping abilities of healthcare providers during the COVID-19 pandemic, drawing parallels between their experiences and those of war veterans; however, this study also lacked empirical substantiation [15].

Considering that homelessness also poses significant challenges to human health, including mental health, and our organization’s volunteers had noted that a significant number of PEH had turned to spirituality as a coping mechanism to deal with the mental health challenges brought about by the COVID-19 pandemic, we hypothesized that imparting the teachings of the Bhagavad Gita as a one-time intervention could enhance the psychological resilience of PEH.

This study aims to bridge the knowledge gap concerning the effectiveness of Hindu RSIs in a previously unexplored population—PEH—by evaluating the impact of learning the Bhagavad Gita on reducing psychological distress among PEH. Engaging in Kuchipudi dance practice as a hobby will function as a positive control, while abstaining from stress-reducing activities will serve as the negative control. In other words, the central research question is, what is the impact of learning the Bhagavad Gita on reducing psychological distress among PEH, and how does this compare with the impact of engaging in Kuchipudi dance practice as a hobby? This multi-site parallel-group RCT seeks to comprehensively assess both short and long-term outcomes. Table 1 outlines the research inquiries guiding our study and presents potential interpretations of the anticipated results.

**Table 1 pone.0310795.t001:** Study design.

Question	Hypothesis	Sampling plan	Analysis plan	Interpretation given to different outcomes
Does learning the Bhagavad Gita reduce psychological distress in people experiencing homelessness	The immediate post-intervention, delayed post-intervention, and long-term follow-up Kessler psychological distress scale scores will be significantly lower than baseline Kessler psychological distress scale scores	54 participants each in the Bhagavad Gita group, Kuchipudi dance group, Both Bhagavad Gita and Kuchipudi dance group, and Control group for 80% power and 5% alpha	The within-group differences will be analysed by repeated measures analysis of covariance, with continued practice and religion as covariates. Subgroup analyses will be conducted by stratifying the participants in each group by age, religion (Hindu, Non-Hindu), educational attainment, and employment. Post-hoc power analyses will be conducted to verify the robustness and reliability of the subgroup analyses	If we find significant within-group differences in the Kessler psychological distress scale scores, it would suggest that learning the Bhagavad Gita has a potential impact on reducing psychological distress in people experiencing homelessness. Additionally, if our subgroup analyses reveal significant differences based on age, religion, educational attainment, and employment, it would imply that the intervention’s effectiveness varies across these subgroups
Is learning the Bhagavad Gita better at reducing psychological distress than engaging in a hobby in people experiencing homelessness	The decrease from baselines to immediately post-intervention, delayed post-intervention, and long-term follow-up Kessler psychological distress scale scores will be significantly larger in the Bhagavad Gita group than in the Kuchipudi dance group	54 participants each in the Bhagavad Gita group, Kuchipudi dance group, Both Bhagavad Gita and Kuchipudi dance group, and Control group for 80% power and 5% alpha	Intergroup differences will be analysed by the generalised estimating equation and analysis of covariance with continued practice and religion as covariates. Subgroup analyses will be conducted by stratifying the participants in each group by age, religion (Hindu, Non-Hindu), educational attainment, and employment. Post-hoc power analyses will be conducted to verify the robustness and reliability of the subgroup analyses	If our hypothesis holds true, it would suggest that learning the Bhagavad Gita is more effective at reducing psychological distress than engaging in a hobby for people experiencing homelessness. By conducting subgroup analyses, we will further investigate if the effectiveness of the intervention varies based on age, religion, educational attainment, and employment
Does continued practice influence the effect of the interventions in people experiencing homelessness	The decrease from baselines to delayed post-intervention and long-term follow-up Kessler psychological distress scale scores will be significantly larger in all intervention groups in participants who continue the practices learned during the intervention compared to that in participants who do not continue the practices learned during the intervention	54 participants each in the Bhagavad Gita group, Kuchipudi dance group, Both Bhagavad Gita and Kuchipudi dance group, and Control group for 80% power and 5% alpha	Participants in each group will be subdivided based on whether or not they continued practice during each follow-up. Repeated measures analysis of variance will be conducted on the subgroups	If our hypothesis holds true, it would suggest that sustained practice contributes to greater psychological well-being. Conversely, if there are no significant differences in the decrease of the Kessler psychological distress scale scores between participants who continue and those who do not continue the practices, it would indicate that continued practice does not play a significant role in the effectiveness of the interventions
Does learning the Bhagavad Gita provide any added benefit to people experiencing homelessness who are engaging in a recreational activity in terms of reducing their psychological distress	The decrease from baselines to immediately post-intervention, delayed post-intervention, and long-term follow-up Kessler psychological distress scale scores will be significantly larger in the Both group than the Bhagavad Gita and Kuchipudi dance groups	54 participants each in the Bhagavad Gita group, Kuchipudi dance group, Both Bhagavad Gita and Kuchipudi dance group, and Control group for 80% power and 5% alpha	Intergroup differences will be analysed by the generalised estimating equation and analysis of covariance with continued practice and religion as covariates. Subgroup analyses will be conducted by stratifying the participants in each group by age, religion (Hindu, Non-Hindu), educational attainment, and employment. Post-hoc power analyses will be conducted to verify the robustness and reliability of the subgroup analyses	If the reduction in the Kessler psychological distress scale scores is highest in the Both group, it would suggest that learning the Bhagavad Gita combined with engaging in a recreational activity may offer additional benefits in reducing psychological distress among homeless persons compared to learning the Bhagavad Gita group or engaging in a recreational activity alone. This finding would indicate that the combination of the intervention has a more substantial effect on decreasing distress levels

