### Statistical methods

#### Data analysis

All results will be reported in accordance with the CONSORT guidelines to ensure comprehensive and transparent reporting of the trial’s outcomes. Descriptive summaries of baseline characteristics will be presented to provide an overview of the study population. The comparisons will be between each intervention group and the control group, as well as within each intervention group over time. The repeated measures data will be analysed using the generalised estimating equation (GEE) framework. For the analysis of the primary outcome using the GEE framework, robust standard errors will be used to account for correlated data. Pairwise post-hoc comparisons will be conducted to identify specific group differences. To control for the risk of type I error in these multiple comparisons, the Bonferroni correction will be applied. Subgroup analysis will be conducted using analysis of covariance (ANCOVA) or non-parametric ANCOVA [19] depending on the normality of the data; this may include stratification by age, educational attainment, religion, and employment status. Multiple comparisons will also be addressed using appropriate statistical corrections. These may include the Bonferroni correction, Holm’s adjustment, or the Benjamini-Hochberg procedure, depending on the specific comparisons and the number of tests conducted. The data analysis will be conducted using Python 3.9.13. Statistical significance will be set at a two-tailed p < 0.05.

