### Primary analysis

GEE Framework: The primary outcome, psychological distress as measured by the K10 scale, will be analyzed using the GEE framework. Robust standard errors will be used to account for correlated data due to repeated measures. An exchangeable correlation structure will be assumed.Primary Comparisons: Comparisons will be made between each intervention group (Gita, Kuchipudi, and Both) and the control group. Within each intervention group, comparisons over time (pre-intervention, immediate post-intervention, 40 days post-intervention, and 1-year post-intervention) will be performed.Pairwise Post-Hoc Comparisons: Pairwise post-hoc comparisons will be conducted following significant GEE results to identify specific group differences. The Bonferroni correction will be applied to control for the risk of type I error in these multiple comparisons.

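### Table 1's hypothesis tests do not match the GEE designated as the primary analysis, and they adjust for continued practice, which is measured after randomisation

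*Protocol article*

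**What the plan says.** The article describes the analysis of the K10 in two places.

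**Table 1 (Introduction)** gives each research question its own analysis.
- Row 1, change within the Gita arm: "The within-group differences will be analysed by repeated measures analysis of covariance", adjusting for religion and continued practice.
- Rows 2 and 4, Gita against Kuchipudi and Both against each single intervention: "Intergroup differences will be analysed by the generalised estimating equation and analysis of covariance with continued practice and religion as covariates".
- Row 3, continued against discontinued practice: "Repeated measures analysis of variance will be conducted on the subgroups".

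**The abstract and the statistical sections** give one framework. The abstract says "The K10 scores will be analyzed using the Generalized Estimating Equation framework". Data analysis sets the comparisons, "The comparisons will be between each intervention group and the control group, as well as within each intervention group over time", and then assigns the repeated measures to GEE. Primary analysis says "The primary outcome, psychological distress as measured by the K10 scale, will be analyzed using the GEE framework", with robust standard errors and an exchangeable correlation. Under that same heading it lists each intervention against control and the within-arm comparisons over the four time points. It names no covariate. ANCOVA has a different job there: "Subgroup analysis will be conducted using analysis of covariance (ANCOVA) or non-parametric ANCOVA", repeated under Subgroup analyses.

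Outcomes and measures states that continued practice is asked about at the three visits after the intervention. Its meaning depends on the arm: choreography, self-reflection, both, or none for controls.

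**The concern.** Table 1 is where this registered report links each hypothesis to a test, and its last column states what will be concluded from the result. If that test differs from the one in Primary analysis, the conclusion can depend on which part of the article is followed, and the choice can be made after the results are known.

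The two routes are not interchangeable. Repeated-measures ANCOVA and GEE handle incomplete follow-up and the within-person correlation differently. Adding continued practice also changes the quantity estimated. Part of any lasting benefit may act through people keeping up what they learned, and adjustment removes that part. Less distressed participants may also be the ones who keep practising, in which case adjustment can introduce bias as well.

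**Working it through.** No figure in the plan is specific to this point, so the check is mainly a comparison of text.

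**Step 1. Model by hypothesis.**

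| Table 1 row | Table 1 model | Statistical sections | Status |
|---|---|---|---|
| 1: within-arm change, Gita | Repeated-measures ANCOVA; continued practice and religion | GEE; no covariate named | Direct mismatch |
| 2: Gita v Kuchipudi | GEE and ANCOVA; same covariates | GEE; reached only as a post-hoc pairwise comparison; ANCOVA for subgroups | GEE shared; ANCOVA unranked |
| 3: continued v discontinued practice | Repeated-measures ANOVA in subgroups | No analysis given | Unmatched, not contradicted |
| 4: Both v Gita, Both v Kuchipudi | As row 2 | As row 2 | As row 2 |

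The contrasts also differ. The between-arm comparisons listed in Primary analysis are each intervention against control. The contrasts in rows 2 and 4 arise there only through pairwise tests that follow a significant GEE result.

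**Step 2. Could the extra models be sensitivity analyses?** Sensitivity analyses allows alternative models and gives mixed-effects models as its example. It does not say that Table 1's analyses have that role. Table 1 presents them as the analysis that feeds its interpretation column.

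**Step 3. The covariate.** Continued practice has no baseline value and up to three follow-up values, and Table 1 does not say which enters the model. In rows 2 and 4 it also records a different activity in each arm. Because it follows randomisation and can respond to the assigned intervention, a model containing it does not estimate the same effect as a model without it. The documents give nothing from which to size the resulting bias.

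**Step 4. Participants used.** With the stated 16% dropout and 64 per arm:
- 0.16 × 64 = 10.24, about 10 per arm
- 0.16 × 256 = 40.96, about 41 in all

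Standard repeated-measures ANCOVA drops a person with any missing visit, whereas GEE can use that person's earlier visits. These counts are therefore the possible difference between the two analyses, but only if missing visits are not imputed and the GEE uses all available visits.

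**Step 5. False-positive risk if either result could be reported.** For two tests of one null hypothesis at two-sided 5%, independence gives 1 − 0.95² = 0.0975. For correlated test statistics (simulated, normal):

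| Assumed correlation | Chance that at least one is significant |
|---|---|
| 0.99 | 0.057 |
| 0.9 | 0.070 |
| 0.7 | 0.083 |
| 0.5 | 0.091 |

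The documents give no correlation. Two models of the same K10 data would usually be highly correlated, which points to the upper rows.

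**The case against.** The strongest reply is that the primary analysis is not in doubt. The abstract, Data analysis, Primary analysis and the sample size section all point to GEE, and Table 1 calls none of its analyses primary. That stands. A reader might infer that the trial has two conflicting primary analyses, and the documents do not support this.

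Other stronger readings also fail:
- **An unadjusted GEE.** Primary analysis names no covariates but does not exclude them. That it is unadjusted would be an inference from silence.
- **A conflict over row 3.** The SAP sections contain no analysis of that question, so there is nothing for the ANOVA to contradict.
- **Continued practice confounded with arm because controls have none.** No four-arm ANCOVA is stated. Row 1 concerns the Gita arm, and rows 2 and 4 compare active arms only.
- **About 10 per arm lost.** Handling of missing data plans multiple imputation, particularly above 5% missing, and imputed data could feed either model. The plan for missing data and protocol deviations still leaves complete-case analysis open, so the loss is possible but not established.
- **A doubled error rate.** Nothing says that either result may be reported. Bonferroni is planned for pairwise comparisons, although it does not address two models testing one contrast.

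Row 1 survives all of this: the same within-arm comparisons have a different model and covariates in the two places. In rows 2 and 4, an ANCOVA that the statistical sections keep for subgroups stands beside GEE with no order of precedence.

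**Conclusion.** The point holds as a mismatch between Table 1 and the designated primary analysis. It is direct for row 1. For rows 2 and 4 it is an unranked second test together with covariates absent from Primary analysis. Row 3 is merely unmatched.

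The most consequential part is continued practice as a covariate, since including it changes what rows 1, 2 and 4 estimate and can bias the result. That rests on its timing, which the article states, and not on any assumed number.

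The numerical consequences are conditional. The false-positive chance would be about 6% to 10% over the full range of assumed correlations, and only if either result could be reported. Up to about 10 of 64 per arm could count in one analysis and not the other, and only without imputation.

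**What to change.** Use one model, one covariate set and one list of contrasts per hypothesis, worded identically in Table 1 and Primary analysis:
- **Deciding model:** make the GEE in Primary analysis the only deciding model for rows 1, 2 and 4.
- **Row 1:** Gita against Control in change from baseline, a comparison Primary analysis already lists. Within-arm changes can still be reported from the same model.
- **Row 2:** Gita against Kuchipudi.
- **Row 4:** Both against Gita, and Both against Kuchipudi. The Bonferroni correction now planned for pairwise comparisons should stay with rows 2 and 4 once they are named.
- **Covariates:** drop continued practice from these effect analyses. Keep religion only if it is named in both places.
- **ANCOVA:** label any that remains as sensitivity or subgroup analysis.
- **Row 3:** label it exploratory, because continuing to practise is not randomised.

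The change touches hypotheses and models as well as wording. Under Ethical considerations, the cost is a new protocol version, an update to the registry entry and notice to the ethics committee. Recruitment, visits and data collection are unaffected, and there are fewer analyses to run.

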### Subgroup analyses

ANCOVA/Non-Parametric ANCOVA: Subgroup analyses will be conducted using ANCOVA or non-parametric ANCOVA depending on the normality of the data. Subgroups may include stratification by age, educational attainment, religion, and employment status.Multiple Comparisons: To address the risk of type I error due to multiple comparisons, appropriate statistical corrections will be applied, which may include the Bonferroni correction, Holm’s adjustment, or the Benjamini-Hochberg procedure.

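### Table 1 infers varying effectiveness from stratified within-group analyses and relies on post-hoc power to confirm subgroup results; no interaction test is named

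*Protocol article*

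**What the plan says.** Table 1 (in the Introduction) sets out the subgroup plan in rows 1, 2 and 4: "Subgroup analyses will be conducted by stratifying the participants in each group by age, religion (Hindu, Non-Hindu), educational attainment, and employment". Each of these rows adds: "Post-hoc power analyses will be conducted to verify the robustness and reliability of the subgroup analyses".

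The rows differ in what is analysed and concluded:

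- **Row 1** (does learning the Gita reduce distress) is a within-group analysis over time by repeated measures ANCOVA. Its interpretation column says that if subgroup differences are significant, "it would imply that the intervention’s effectiveness varies across these subgroups".
- **Row 2** (Gita against Kuchipudi) uses GEE and ANCOVA between groups. It presents the subgroup work as further investigation of whether effectiveness varies.
- **Row 4** (Both against each single intervention) also compares groups, and interprets no subgroup result.

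Other sections are looser. The Abstract gives the aim as "to explore potential differential effects using analysis of covariance". Under Data analysis, "this may include stratification by age, educational attainment, religion, and employment status". The Subgroup analyses section of the SAP part says: "Subgroup analyses will be conducted using ANCOVA or non-parametric ANCOVA depending on the normality of the data". It also promises corrections for multiple comparisons, "which may include the Bonferroni correction, Holm’s adjustment, or the Benjamini-Hochberg procedure". No section names a group-by-subgroup interaction.

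**The concern.** There are two faults in what is stated, and one risk that depends on how the text is read.

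1. **Row 1 cannot support its conclusion.** K10 scores can fall differently in, say, older and younger Gita participants because their distress would have taken different courses anyway. A contrast within one arm cannot separate that from a different effect of the intervention. The trial has a no-intervention control arm, but row 1 does not use it.

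2. **Post-hoc power is not a check.** Power computed from the observed effect is a function of the p-value. A chance finding that reaches significance will always show at least 50% observed power, so the planned safeguard would lend support to false subgroup findings.

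3. **The risk.** If strata are tested separately and the results set side by side, one significant and one non-significant result could be reported as effect modification when the effect is the same in both.

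At stake are published statements about which homeless people benefit. The primary comparisons are not affected.

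**Working it through.** **The plan's own figure.** The document gives no figure for subgroup error or subgroup power. Its only power statement (Sample size calculation) is 80% at two-sided 5% with 54 per group and a difference of 7 points. That derivation does not reproduce. V_eff = 55/(1 + 3 × 0.5) = 22.0, where 22.5 is printed. The printed formula gives (1.96 + 0.84)² × 22.5/(7² × 0.5²) = 7.84 × 22.5/12.25 = 14.4, not 53.3 (14.1 with 22.0). No SD is stated. The 80% is therefore used below only as the sponsor's target.

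**Row 1, both readings.**
- Strata judged by separate significance: one significant and one non-significant result is not evidence that the two differ.
- Strata compared directly: the quantity compared is change over time in Gita participants, which is natural course plus effect. A difference may lie in either part.

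On either reading the stated conclusion does not follow.

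**Post-hoc power.** Observed power = Φ(z_p − 1.96), where z_p is the z-value matching the two-sided p-value (the opposite tail is negligible).
- p = 0.05: Φ(1.96 − 1.96) = 0.50
- p = 0.005: Φ(2.81 − 1.96) = 0.80

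The p-value alone fixes the answer. This step needs no assumption about effect size or SD.

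**Separate testing of strata (conditional).** Assume a between-group comparison, the same true effect in every stratum, 80% full-group power, and a reading of one stratum significant and the other not. The full-group noncentrality is 1.96 + 0.84 = 2.80. For a stratum holding a fraction f of participants:

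stratum power = Φ(2.80 × √f − z)

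P(exactly one significant) = p1(1 − p2) + p2(1 − p1)

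| Setting | Stratum powers | Exactly one significant |
|---|---|---|
| 50/50 split, alpha 0.05 | Φ(1.98 − 1.96) = 0.508 each | 2 × 0.508 × 0.492 = 0.50 |
| 80/20 split, alpha 0.05 | 0.707 and 0.240 | 0.61 |
| 50/50 split, alpha 0.05/8 | 0.226 each | 2 × 0.226 × 0.774 = 0.35 |
| No effect, alpha 0.05 | 0.05 each | 2 × 0.05 × 0.95 = 0.095 |
| No effect, alpha 0.05/8 | 0.00625 each | 0.012 |

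The divisor 8 (four factors with two strata each) is an illustration, because the plan does not fix its correction. With an even split and unadjusted alpha, full-group power of 50% gives 0.41, 90% gives 0.47 and 99% gives 0.24.

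A simulation of 40,000 two-arm trials (54 per arm, SD assumed to be 12.98 so that a 7-point difference has 80% power) gave 0.499 for the 50/50 split and 0.610 for 80/20.

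**Interaction test instead.** In the same simulation a treatment-by-subgroup interaction test gave a false difference in 5.0% (50/50) and 5.1% (80/20) of trials. Four unadjusted independent tests would give 1 − 0.95⁴ = 18.5%, so the promised correction is still needed.

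**What the interaction test can detect.** If the full effect were present in one of two equal strata and absent in the other, the interaction noncentrality is 2.80/2 = 1.40, and power is Φ(1.40 − 1.96) = 0.29.

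**The case against.** The strongest reply is that no section states a rule of judging one stratum significant and the other not. Row 1 speaks of significant differences between subgroups, which with ANCOVA can mean a direct comparison of strata. The Abstract calls the aim exploratory, Data analysis makes stratification optional, and a multiplicity correction is promised. This is also a condensed article, and exact model terms are commonly left to a fuller plan. Only row 1 draws an explicit conclusion about effect modification.

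Much of this stands, and it limits what may be claimed. A reader might infer more in three ways:

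- **That the plan will produce false subgroup differences half the time.** The documents do not support this as a general rate. It needs the inferred reading, a real uniform effect, 80% full-group power, equal strata and unadjusted alpha. It also does not describe row 1 itself, since the document gives nothing from which within-group stratum power could be derived.
- **That the rate compounds over four factors as if they were independent.** It does not, because all four factors re-split the same participants and share one overall treatment estimate.
- **That a religion-specific claim is what the study is designed to make.** Religion is one of four listed factors. The central question is the effect of learning the Gita and how it compares with Kuchipudi.

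The reply does not rescue row 1, which fails on either reading, or the post-hoc power sentences. Those are stated rules and not missing detail. The silence on interaction terms would not be a finding by itself; it matters because the article already publishes an inference that needs them.

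**Conclusion.** The point holds, and the plan should be changed. Two parts rest on the text alone: row 1's inference from within-group strata to varying effectiveness is invalid, and the post-hoc power named in rows 1, 2 and 4 cannot confirm a subgroup result.

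The numerical size is conditional. Under separate significance testing of two equal strata, with a uniform effect and the sponsor's target of 80% power, about 50% of trials would look discordant for a given factor. A correction at 0.05/8 lowers this to about 35%. With no effect it is about 10% unadjusted and about 1% corrected. One interaction test gives 5% under a uniform effect. The 80% is itself unsupported by the printed sample size arithmetic, so these figures show the order of the problem and do not predict this trial's error rate.

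The consequence is confined to secondary, exploratory claims.

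**What to change.** - Rest any statement that effectiveness varies on group-by-subgroup (by time) interaction terms in the planned GEE. Do this for the between-group comparisons already planned: each intervention against control, Gita against Kuchipudi, and Both against each single intervention.
- Apply the promised multiplicity correction to these interaction tests, with the method and the family of tests fixed in advance.
- Report stratum estimates with confidence intervals, labelled exploratory.
- Reword the interpretation in row 1 so that a claim of varying effectiveness depends on the interaction result and not on within-group strata.
- Delete the post-hoc power sentences in rows 1, 2 and 4.

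The cost is wording and a few model terms, with no new data, visits or participants. The price is more cautious subgroup conclusions. Even a full effect in one half and none in the other would be detected with only about 29% power under the 80% target, so a non-significant interaction must not be read as showing equal effects.
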